## Abstract

**Background:**

The clinical manifestation of COVID-19 is associated with infection and inflammation of the lungs, but there is evidence to suggest that COVID-19 may also affect the structure and function of the cardiovascular system. At present, it is not fully understood to what extent COVID-19 impacts cardiovascular function in the short- and long-term following infection. The aim of the present study is twofold: (i) to define the effect of COVID-19 on cardiovascular function (i.e. arterial stiffness, cardiac systolic and diastolic function) in otherwise healthy individuals and (ii) to evaluate the effect of a home-based physical activity intervention on cardiovascular function in people with a history of COVID-19.

**Methods:**

This prospective, single-centre, observational study will recruit 120 COVID-19-vaccinated adult participants aged between 50 and 85 years, i.e. 80 with a history of COVID-19 and 40 healthy controls without a history of COVID-19. All participants will undergo baseline assessments including 12-lead electrocardiography, heart rate variability, arterial stiffness, rest and stress echocardiography with speckle tracking imaging, spirometry, maximal cardiopulmonary exercise testing, 7-day physical activity and sleep measures and quality of life questionnaires. Blood samples will be collected to assess the microRNA expression profiles, cardiac and inflammatory biomarkers, i.e. cardiac troponin T; N-terminal pro B-type natriuretic peptide; tumour necrosis factor alpha; interleukins 1, 6 and 10; C-reactive protein; d-dimer; and vascular endothelial growth factors. Following baseline assessments, COVID-19 participants will be randomised 1:1 into a 12-week home-based physical activity intervention aiming to increase their daily number of steps by 2000 from baseline. The primary outcome is change in left ventricular global longitudinal strain. Secondary outcomes are arterial stiffness, systolic and diastolic function of the heart, functional capacity, lung function, sleep measures, quality of life and well-being (depression, anxiety, stress and sleep efficiency).

**Discussion:**

The study will provide insights into the cardiovascular implications of COVID-19 and their malleability with a home-based physical activity intervention.

**Trial registration:**

ClinicalTrials.gov NCT05492552. Registered on 7 April 2022.

**Supplementary Information:**

The online version contains supplementary material available at 10.1186/s13063-023-07360-7.

## Introduction

Severe acute respiratory syndrome coronavirus 2 (SARS-CoV-2) caused the coronavirus disease outbreak (COVID-19) in 2019 [1]. The virus spread worldwide and was declared a pandemic by the World Health Organization (WHO) [2]. COVID-19 presents as an acute respiratory infection with symptoms ranging from mild to severe [3]. This highly infectious disease has claimed an estimated six million deaths worldwide [4]. COVID-19 transmission occurs directly through respiratory droplets (aerosol and droplet) and indirectly through faecal-oral routes.

Whilst the virus primarily affects the respiratory system, there has been evidence to suggest effects on other organ systems including the cardiovascular system [5]. Pre-existing conditions such as hypertension, cardiovascular disease (CVD), obesity, diabetes, renal disease, chronic respiratory disease, tumours or cancers are associated with higher severity and increased fatality of COVID-19 infection [6].

Many reports have highlighted that COVID-19 with cardiovascular involvement leads to poor prognosis and outcomes [7, 8]. A fivefold increase in the death rate in those with pre-existing CVD was reported [6]. A previous study found myocardial injury was associated with the increased fatality of COVID-19, with inflammation being a potential mechanism for myocardial injury [9]. Limited number of studies reported the cardiovascular effects of COVID-19 in previously healthy individuals.

To maintain overall health, physical activity has been beneficial to accelerate recovery in chronic conditions [10]. The importance of exercise has been highlighted in many studies for the prevention and rehabilitation of cardiovascular function. Liu et al. outlined that rehabilitation may cause respiratory muscle strengthening and improvement of respiratory system function [11]. Physical activity can improve health in low-grade inflammation (associated with ageing) and COVID-19 [12–16]. The WHO highlighted that home-based physical activity provides a safe, cheap and controllable intervention for all ages affected by COVID-19 [17]. Home-based physical activity has been shown to reduce blood pressure [18] and improve quality of life (QoL) [19]. Given the novelty of this virus, there is a lack of research on physical rehabilitation post-COVID-19 infection. As some individuals presented with COVID-19 pneumonia, home-based exercise in the elderly improved cardiac peak flow and physical function which prevented aspiration pneumonia [20]. Tang et al. found that a home-based exercise programme improved the functional capacity and overall quality of life in those discharged after being admitted with COVID-19 [21]. A case report showed exercise rehabilitation improved the 6-min walk test and stress test results where the patient had oxygen (O_2_) desaturation in the initial testing [22]. Similarly, Stavrou et al. demonstrated that 8 weeks of an unsupervised rehabilitation program can improve many symptoms of long COVID-19 syndrome [23]. Previous studies have also found that a 6-month home-based cardiac rehabilitation for breast cancer patients was safe, improved peak O_2_ consumption and overall physical fitness and is an effective method to encourage participation in physical activity [24]. Improvement in QoL, exercise tolerance and haemodynamic function was also reported following a home-based physical activity intervention in middle-aged to older individuals with heart failure [25]. More recently, studies have shown that home-based physical activity intervention improves exercise capacity and enhances recovery and QoL in COVID-19 survivors [26, 27].

Cardiovascular involvement in healthy individuals with a history of COVID-19 infection is still uncharacterised. It is important to investigate the initial signs of changes in cardiovascular structure and function to improve understanding of the effects of this novel disease. This can inform health care services by providing evidence for the need for comprehensive cardiovascular screening and early interventions to prevent deterioration if cardiovascular function in people with a history of COVID-19.

The present study is designed to evaluate the effects of COVID-19 on cardiovascular structure and function and to determine their amelioration with physical activity. The aim of the present study is twofold: (i) to define the effect of COVID-19 on cardiovascular function (i.e. arterial stiffness, cardiac systolic and diastolic function) in otherwise healthy individuals and (ii) to evaluate the effect of a home-based physical activity intervention on cardiovascular function in people with a history of COVID-19. We will test the following two hypotheses: (i) cardiovascular function will be significantly reduced in people with a history of COVID-19, and (ii) a home-based physical activity intervention will significantly improve cardiovascular function and quality of life in people with a history of COVID-19.

## Methods

### Study design, setting and ethics

The present single-centre, prospective, observational and interventional, randomised controlled study will be undertaken at the Coventry University Cardiovascular Research Laboratory between January 2022 and August 2023.

Ethical approval was granted by the Coventry University Research Ethics Committee (P125303) and the UK Health Research Authority National Health Service East Midlands – Leicester South Research Ethics Committee (22/EM/0090). The study will be conducted in accordance with the Declaration of Helsinki. The study was prospectively registered on ClinicalTrials.gov (NCT05492552) on 7 April 2022. The participant timeline is shown in Fig. 1.

**Fig. 1 Fig1:**
[figure not shown]
Study timeline: time schedule of enrolment, intervention and assessment for visits 1 and 2. ECG, electrocardiogram; CPEX, Cardiopulmonary exercise stress test; HRV, heart rate variability; wk., week

### Sample size

One hundred twenty participants aged between 50 and 85 years will be recruited for the study. This will include 80 participants with a history of COVID-19 and 40 healthy individuals without a history of COVID-19 to complete baseline assessments. Additionally, participants with a history of COVID-19 will be randomly assigned (1:1) to either a 12-week home-based physical activity intervention or usual care control group. The study design is outlined in Fig. 2. The primary outcome measure is LV GLS, as a measure of cardiac systolic function. With a type I error of 0.05 and an intended high power of > 90%, 40 participants per group are required to detect a 3% difference in LV GLS between the COVID-19 and non-COVID groups. In response to the physical activity intervention within the COVID-19 group, assuming a standard deviation of 2.5% and an estimated attrition rate of ~ 20% in the intervention period of the study, 40 participants per group will be required, providing the overall recruitment target of 80 participants with a history of COVID-19.

**Fig. 2 Fig2:**
[figure not shown]
Study design, inclusion and exclusion criteria

### Randomisation

Randomisation numbers will be generated by secure web-based randomisation to maintain concealment and minimise selection bias. The randomisation process will be performed by the researchers, and the principal investigator will generate the randomisation numbers. A randomisation sequence was computer generated, with each allocation assigned a number. Following baseline testing, each participant was asked to pick out a number from an opaque box. Participants were blinded to their allocation to ensure a ‘usual’ baseline week was obtained; however, due to the nature of the intervention, researchers (i.e. outcome assessors and analysts) were unblinded to the allocation.

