#### Cardiovascular function

Cardiac and vascular parameters will be assessed at rest and peak cardiopulmonary exercise using non-invasive methods (Starling SV – Baxter Healthcare Ltd., USA) and echocardiogram. An echocardiogram will be performed using ultrasound to acquire 2D real-time images of the heart to assess cardiac structure and function (Vivid IQ, GE Healthcare, USA). Participants will be asked to undress to the waist, and gowns will be offered to all participants. An ultrasound probe will be placed on the chest with lubricating gel to form good contact between the probe and skin for image acquisition. Echocardiography will be performed at rest and at peak exercise.

Arterial stiffness, a measure of arterial function, will be assessed at rest using non-invasive gold standard techniques which allows for both pulse wave analysis (PWA) and pulse wave velocity (PWV)measurements (Sphygmacor device; AtCor Medical, NSW, Australia). A blood pressure cuff will be placed on the participants’ upper left arm for PWA assessment. For PWV assessment, a tonometer will be placed against the neck and a blood pressure cuff will be placed on the upper thigh to simultaneously measure carotid artery pulse wave velocity and femoral artery blood pressure.

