### Intervention

#### Physical activity intervention group

The exercise intervention group will undergo a 12-week home-based physical activity intervention. The participants will be asked to increase their daily steps by at least 2000 steps per day from baseline, e.g. walking for approximately 30 min in addition to baseline, 5 days a week. A large cohort study of 9306 participants demonstrated that an incremental increase in physical activity of 2000 steps per day reduced the risk of cardiovascular events by 10% [30]. A pedometer will be provided to all participants with a diary sheet to record the number of steps per day. Weekly telephone calls lasting 10–15 min each will be made to each participant in the intervention group to provide an opportunity for the participants to ask any questions and for the research staff to encourage the participant to achieve their step goal. Suitable days and times will be arranged for phone calls to take place. After the intervention period, i.e. 13 weeks from the date of the initial visit, participants will be invited to visit the laboratory for follow-up assessments. One week will be allowed for the participants to record their baseline step count. On the first day of the second week, researchers will contact the participant to inform them of which group they have been allocated to. The same outcomes will be measured during the follow-up visit to determine a value of change.

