### Outcome measures

The primary outcome measure is mean change in left ventricular global longitudinal strain after 12 weeks of the study intervention. Secondary outcomes are mean changes from baseline to the end of the intervention period in arterial stiffness (pulse wave velocity and augmentation index), measures of systolic and diastolic function of the heart (i.e. left ventricular ejection fraction, cardiac output, stroke volume, cardiac power, early-to-late filing ratio, right ventricular global longitudinal strain, left atrial strain, ventricular-arterial coupling, right ventricular diastolic function), heart rate variability, functional capacity, lung function, inflammatory and cardiac biomarkers, quality of life and well-being (depression, anxiety, stress, fatigue and sleep measures). Sleep measures include bedtime (h:min), wake-up time (h:min), time-in-bed (h), total sleep time (h), sleep onset latency (min), sleep efficiency (%), number of awakenings and wake after sleep onset (WASO, min), number and timing of naps, inter-daily variability and stability (as markers of circadian rhythmicity), and timing and nature of light exposure during a 24-h period. Additionally, we will assess the differences in the COVID-19 group vs. the non-COVID-19 group.

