### Data collection storage and monitoring

Data will be collected by the research team members, and only individuals authorised by the chief investigator will have access to the data. All data will be processed in accordance with the General Data Protection Regulation 2016 and the Data Protection Act 2018. Data will be given a unique participant identification number. Data will be documented in paper-based case report form (CRF), all data will be uploaded to an access-controlled OneDrive folder from a password-protected computer and all paper documents will be stored in a locked cabinet. Data entry will be checked by two of the research team members to minimise errors. Data will be archived in accordance with institutional guidelines after study closure and will be stored up to 5 years. No formal data monitoring committees have been organised for this study. Research team members, led by the chief investigator, will monitor the study throughout the period of the research study.

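### The nature of a walking programme does not explain why the strain reader and the analyst must know the randomised arm, so the primary outcome is open to avoidable reader bias

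*Protocol article*

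**What the plan says.** The Randomisation section says that participants did not know their arm while the baseline week was recorded, and then that "due to the nature of the intervention, researchers (i.e. outcome assessors and analysts) were unblinded to the allocation". No other reason is given.

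The Outcome measures section fixes the endpoint: "The primary outcome measure is mean change in left ventricular global longitudinal strain after 12 weeks of the study intervention". The Abstract lists "rest and stress echocardiography with speckle tracking imaging" among the assessments, and the Cardiovascular function section says that "An echocardiogram will be performed using ultrasound to acquire 2D real-time images of the heart to assess cardiac structure and function".

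The intervention itself is described under Physical activity intervention group: "The participants will be asked to increase their daily steps by at least 2000 steps per day from baseline". Contact with staff differs by arm: "Weekly telephone calls lasting 10–15 min each will be made to each participant in the intervention group".

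The safeguards named under Data collection storage and monitoring are a check of data entry by two team members and oversight by the research team. The same section adds that "No formal data monitoring committees have been organised for this study".

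**The concern.** Blinding of participants, of treating staff, of outcome readers and of analysts are four separate questions. The article answers the last two with a reason that bears only on the first two. Participants must know whether they have been asked to walk more, and the staff who encourage them by telephone must know as well. Nothing in the intervention requires the person who derives strain from an image, or who runs the analysis, to know it.

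This matters because the hypothesis is directional: the article expects the intervention to improve cardiovascular function. A reader who knows the arm and the visit can, without intending to, shift the measurement in the expected direction. Such a shift adds directly to the estimated treatment effect. A larger sample does not reduce it, and no later analysis can separate it from a true effect. An unmasked analyst is a lesser but similar exposure, since the choice between parametric and rank tests is to be made on the data.

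**Working it through.** **Text check.** The article states no figure on this point, so there is none to reproduce. Setting the sections side by side:

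| Who | Does the nature of the intervention make knowledge of the arm unavoidable? | What the article provides |
|---|---|---|
| Participant | Yes, once told in week 2 | Masked during the baseline week |
| Staff making weekly calls | Yes, only the intervention arm is called | Unmasked |
| Person measuring strain | No, strain is derived from acquired images | Unmasked |
| Analyst | No, arms can be labelled A and B | Unmasked |

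No section mentions masked, independent or duplicate reading, or a masked analyst. The double check of data entry guards against transcription errors. It does not protect a strain value that was read with knowledge of the arm.

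**Illustration of what is at stake.** Inputs:
- SD 2.5 GLS points (Sample size, for the randomised comparison). The article does not say whether this is the SD of a single value or of a change; I apply it to the quantity compared between arms.
- 40 per arm and about 20% attrition (Sample size): 40 × 0.8 = 32 completers per arm.
- Type I error 0.05 (Sample size: "With a type I error of 0.05 and an intended high power of > 90%, 40 participants per group are required"). Two-sided is assumed, as the article does not state it.
- No true effect, and a systematic between-arm reading shift b. The values of b are assumptions.

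Standard error of the difference: SE = 2.5 × √(2/32) = 0.625.

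Under a two-sample t-test with 2 × 32 − 2 = 62 degrees of freedom (critical value 1.999), the false-positive rate is the probability that a noncentral t with noncentrality b/SE lies beyond ±1.999.

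| Assumed shift b | b/SE | False-positive rate |
|---|---|---|
| 0.25 | 0.4 | 6.8% |
| 0.5 | 0.8 | 12.4% |
| 0.75 | 1.2 | 21.9% |
| 1.0 | 1.6 | 35.0% |

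A normal approximation, P(|Z + b/SE| > 1.96), gives 6.9%, 12.6%, 22.4% and 36.0%, so the result does not depend on the method.

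With all 40 per arm retained, SE = 2.5 × √(2/40) = 0.559. The t-test rates for shifts of 0.5 and 1.0 rise to about 14% and 42%. More participants make a fixed reading bias more likely to reach significance.

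For scale, 0.5 points is one-sixth of the 3-point difference in the Sample size section (0.5/3 = 0.17). The article ties that difference to the COVID versus non-COVID comparison.

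**The case against.** The strongest reply is that the protocol discloses the unblinding openly, and that nothing in it shows that reader bias occurred or how large it might be. That is correct. The false-positive rates depend entirely on assumed shifts, and at the smallest one shown the inflation is modest, from 5% to about 7%. They are also computed for a between-arm t-test, whereas the Data analysis methods section names only paired pre/post tests for the intervention and independent-samples tests only for COVID versus non-COVID. The table shows sensitivity and does not estimate this trial's error rate.

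Four stronger readings are tempting, and the article does not support them:

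- *That the COVID versus non-COVID contrast is biased in the same way.* The statement concerns the randomised allocation. COVID status is not allocated, numbers are drawn after baseline testing, and the arm is announced in week 2. Readers may well know COVID status, but the article does not say so.
- *That the people who make the encouragement calls also read the images.* The article speaks of researchers, research staff and the research team without separating roles. It does not say that the same individuals do both.
- *That stored loops and subjective reader choices are documented.* The article says that 2D images are acquired and that speckle tracking is used. Retention of loops, offline analysis and the scope for reader judgement are inferences from general knowledge of the method.
- *That the inflation is larger still after baseline adjustment.* A smaller residual SD would have that effect, but the article names no such adjustment and gives no such SD.

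It is also fair to object that coded reading is only a partial remedy. Whoever acquires the follow-up images may still know the arm, and a reader who acquired or has already read an image may recognise it.

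What remains after all this is the explicit statement and a reason that does not support it. Because the article fixes the choice in words, it cannot be treated as a detail left to a fuller protocol or analysis plan.

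**Conclusion.** The point holds for the randomised comparison. The article leaves outcome assessors and analysts unblinded and justifies this with a reason that applies to participants and calling staff only. The primary outcome is therefore exposed to a reader bias that could largely be avoided.

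That the stated reason fails is certain from the text. The size of the consequence is not known. Under the assumptions above, it runs from a slight inflation of the type I error (about 7% at a 0.25-point shift) to a serious one (about 35% at 1.0 point). That masked reading is feasible rests on the assumption that echo loops are retained. This is a cheap improvement worth making. It is not evidence that any result is biased.

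**What to change.** Amend the Randomisation section to separate the roles. State that participants and staff in contact with them cannot be masked after the baseline week, and that strain measurement and the primary analysis are masked. Specifically, assuming echo loops are retained:

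1. A team member codes the loops and removes participant ID, arm and visit date.
2. The existing reader measures strain on the coded loops in random order, with baseline and follow-up mixed, and locks the values before the code is broken. Images already read are re-coded and re-read.
3. The primary analysis is run on arms labelled A and B, and unmasked only afterwards.
4. The article acknowledges that bias from unmasked acquisition of follow-up images remains.

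Hiding COVID status under the same coding is a sensible extension for the baseline contrast. It goes beyond what the Randomisation section addresses.

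Cost: coding and reading or re-reading time for up to 200 examinations (120 at baseline plus 80 at follow-up, before attrition), and somewhat later results. No additional reader, visit or procedure is needed.
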